##### Language development (4 years)

The Peabody Picture Vocabulary Test, 4^th^ Edition (PPVT-4; [145]) will be used to assess receptive vocabulary (comprehension). The researcher presents the child with a book containing four pictures per page and asks the child to point to the picture that best represents the vocabulary word. The total number of correctly identified pictures can be converted to a standard score, percentile rank, or mental age.

#### Video recordings and ratings

##### Play levels (16 months and 2½ years)

Children’s play quality is an indirect measure of cognitive development, unencumbered by shyness or other social behaviors that may inhibit children from achieving their full potential when assessed by an examiner. We assess levels of functional play, symbolic play, and play diversity using the Free Play Protocol as per [name], et al. [49]. The children were given the opportunity to play with age-appropriate toys on their own for 10 minutes and were videotaped for later coding and analysis.

##### Emotional availability and attachment relationship (16 months and 2½ years)

Emotional availability [146] is a standardized global measure of the nature of the mother-infant relationship. Mothers and infants engaged in a 10-minute joint play session, a ~3-minute separation, and a 5-minute reunion play session. Mother-child interactions were videotaped for later coding and analysis. Four dimensions of maternal qualities are being coded: sensitivity, structuring, non-intrusiveness, and non-hostility. Two infant qualities are also being coded: responsiveness to the mother and involvement with the mother. The validity and stability of the construct over time have been established [147] and the data can give information about the nature of the relationship between the dyad, in terms of a ‘secure’ or ‘insecure’ attachment relationship.

##### Parental control and rejection (4 years)

Children will be provided with two different and challenging tasks (e.g. jigsaw puzzle, speech task), suitable for children between 5 to 6 years of age such that these tasks would normally be beyond their ability to solve alone. The child will be instructed to complete each task in five minutes while their mother provides support nearby. The task will be video recorded and maternal behavior will be coded for control and rejection, two theoretical concepts that have been implicated in the development of anxiety in children. As per Hudson and Rapee [148], maternal behavior will be rated on 10 global scales, scored on a 9-point continuum from 0 to 8 with 4 being neutral. The 10 scales assess intrusiveness, helpfulness, physical involvement, maternal focus, posture, positive affect, mood, tension, encouragement/criticism, and child’s response to mother [148].

#### Biological samples: mother, birth, and child

##### Maternal pregnancy blood samples (36 weeks gestation)

Women still pregnant at the time of recruitment had additional blood drawn for the purposes of QF2011 at the time of routine antenatal blood tests collected at 36 weeks gestation. An additional 4 × 5ml vials were drawn, centrifuged, then stored at -80°C (plasma and serum). Blood samples will be analyzed for (a) endocrine markers; (b) immune panel (cytokines); and (c) biomarkers of nutrition panel.

##### Maternal diurnal cortisol (recruitment and 12 months post-flood)

At each time point, participants were asked to collect saliva samples over two days at the following times: waking (w), w + 30 min, w + 45 min, w + 60 min, and before bed, taking note of all times and, if applicable, times of breastfeeding before and during sampling [149]. Cortisol concentrations are determined by competitive enzyme immunoassay (EIA) using Salimetrics kits [150, 151].

##### Maternal DNA (16 months, or 2½ years, or 4 years)

Mothers provided a saliva sample for the purposes of genotyping using Oragene DNA OG-500 kits. Saliva for DNA can be stored at room temperature for several years before processing due to the presence of a chemical preservative in the collection tube provided. Women provided saliva for DNA at the 16 month or the 2½ year assessment. If necessary, saliva samples for DNA will be collected at the 4 year assessment from women who had not provided samples previously.

##### Placenta

The placenta was collected within 20 minutes after expulsion then sampled and processed within 60 minutes. Each placenta was inspected (morphology, weight, and cord position, calcification, etc.) before sampling. Chorionic villi biopsies were collected as per a standardized protocol proposed by the International Federation of Placenta Associations [152]. Multistage unbiased random sampling (giving all parts an equal chance of being chosen) of eight pieces, each one 1 cm^3^, was conducted from the fetal side of each placenta to avoid maternal decidual and fetal amnion/chorion membrane contamination [153, 154]. Placental villi samples were snap-frozen then stored at -80°C. Fetal chorion/amnion membrane, decidua, and chorionic villi were also sampled from two sites (center and perimeter) of the placenta, rinsed of blood, snap-frozen, and stored at -80°C.

##### Umbilical cord

The total length of the umbilical cord was measured, and five 1 cm pieces of umbilical cord (in the sterile area) were collected, snap frozen and stored at -80°C.

##### Cord blood

Cord blood was collected following expulsion of the placenta. The umbilical cord was clamped off from the newborn and blood samples were collected from the umbilical vein using a syringe, then transferred to both serum-separating and heparin tubes. Serum and plasma were collected from these tubes, respectively (around 5-10 mL each) and stored at -80°C.

##### Neonatal reactive cortisol (2-4 days postpartum)

Saliva samples were collected from neonates to assess HPA reactivity to a stressor: the routinely administered, but painful, heel prick procedure used to screen neonates for a range of metabolic and other conditions. Samples were taken using Salimetrics SalivaBio Swabs or Salimetrics Cotton Dental Swabs at three time points: immediately before the heel prick (baseline), and 20 and 40 minutes post-heel prick. As per the manufacturer’s instructions the Bioswabs were centrifuged immediately at 3000-3500 rpm for 15 min.

##### Child diurnal cortisol (16 months and 2½ years)

Saliva samples were collected from the children using Salimetrics Children’s Swabs (Item number 5001.06). Mothers were asked to take a total of six saliva samples from their child at waking, 30 minutes after waking, and at bedtime for two consecutive days. Samples were stored in the family refrigerator before being brought in for the testing session where the samples were then stored at -80°C. Concentrations of diurnal salivary cortisol were determined by competitive enzyme immunoassay (EIA) using kits provided by Salimetrics.

##### Child reactive cortisol (16 months and 2½ years)

As noted earlier in the description of the child’s behavioral stress reactivity, there was a mother-child separation during the joint play sessions, during which the mother left her child alone in the room for a period of up to three minutes while being monitored by the mother and research assistant by a one-way mirror. To assess changes in cortisol levels, child saliva was collected using Salimetrics Children’s Swabs immediately before the separation, and 20 minutes after the end of the separation [155].

##### Child testosterone (16 months and 2½ years)

Saliva samples for testosterone were obtained using Salimetrics Children’s Swabs (Item number 5001.06). Mothers collected the sample in the morning and kept them in the family refrigerator. Mothers brought the samples into the lab on assessment day where they were stored in a -80°C freezer. Samples were assayed in duplicate using a highly sensitive enzyme immunoassay.

##### Child DNA samples (2½ years)

Saliva for genotyping was obtained using Oragene DNA collection kit OG-575. This non-invasive collection technique involves placing a sponge into the child’s cheek pouch and gently rubbing it against the child’s gums and inner cheek for about 30 seconds. Once the sponge is saturated with saliva, it is inserted into the V-notch of the collection vial and twisted to allow the saliva to flow downwards. This procedure is repeated until 0.75 mL of saliva is obtained. This procedure yields approximately 17.3 ug of DNA. If necessary, due to missed samples at age 2½, saliva samples for DNA will be collected at the 4 year assessment.

#### Routine database and chart audit

##### Mother’s chart

We requested the extraction of 273 variables from ‘Matrix’, the Mater Mother’s Hospital database. These variables include (but are not limited to): maternal height and pre-pregnancy weight (BMI); all medications prescribed during pregnancy; blood test reports from routine visits (first visit, 16-20 weeks (optional), and 26-28 weeks (incl. glucose tolerance)); and obstetric outcomes.

##### Ultrasound reports

We will obtain any existing ultrasound reports for biometry and growth, blood flow to uterus (uterine arteries), fetus (umbilical vessels), and within the fetus (cerebral arteries). Of particular interest will be the crown-rump length, biparietal diameter, occipitofrontal diameter, and cephalic index, femur and humerus length, head circumference, abdominal circumference, estimated fetal weight, estimated due date, ultrasound gestational age, amniotic fluid index +/- deepest vertical pocket, and umbilical artery Doppler.

##### Baby’s chart

Chart review was performed to collect data on infant sex, as well as birth outcomes including birth weight, length and head circumference, gestational age at birth, one and five minute APGAR scores, and any newborn complications (respiratory distress, infection, congenital anomalies, hypothermia).

#### Data analysis and power

Our analyses of the QF2011 data will proceed in a highly structured manner, according to our underlying explanatory model. This model posits that objective stress and cognitive appraisal predict peritraumatic stress responses, which predict both subjective stress reaction (PTSD symptoms) and maternal HPA axis response. We hypothesize that at least some of these aspects of maternal stress may influence maternal mental health and may also influence variables within the placenta and fetus (cord blood); thereby influencing fetal/child physical/physiological development (growth & body composition, fingerprints or finger length ratios, HPA axis) and child neurodevelopment (cognitive, behavioral, and motor development). We further suggest that at each level of the cascade there may be genetic moderation and epigenetic mediation; and also moderation of outcomes by pre-disaster maternal characteristics (e.g., depression, socioeconomic status), and by the sex of the infant. Finally, our results may indicate a moderating effect from prenatal care (MGP versus standard care) and maternal caretaking behaviors. Below, we present a sampling of statistical approaches we will take to the data analysis.

##### Maternal short-term response to the floods

Our first task is to understand the associations among the psychosocial and biological responses of the mother to the stress of the flood. Associations among objective stress (QFOSS), cognitive appraisal, peritraumatic distress (PDI) and dissociation (PDEQ), PTSD symptoms (IES-R), and maternal diurnal cortisol will be explored using correlations, and trend analyses to determine if any of the associations are non-linear. We will also test the ability of maternal genes associated with the HPA axis to moderate the effects of flood stress on maternal diurnal cortisol after the floods.

##### Maternal mental health

Next, we will examine genetic and psychosocial mediators and moderators of the associations between flood stress and 12-month post-flood maternal outcomes such as symptoms of anxiety (STAI) and PTSD, as well as positive mental health (MHC-SF). We will test the ability of maternal coping style (Brief COPE) and specific candidate genes to moderate the effects of objective stress exposure on mental health outcomes. For women who had the EPDS administered before the floods, we will also determine the moderating effects of pre-flood depression (as measured by the EPDS) in the association between objective stress exposure and maternal mental health outcomes. Our general approach is to use hierarchical multiple linear regression, adding variables into the equation one block at a time. We first regress maternal mental health on exogenous variables such as maternal genotype and demographics; next, we add objective stress exposure; peritraumatic distress and dissociation; then psychosocial variables needed for the interaction (e.g., coping style); and finally we test one interaction at a time (e.g., objective stress-by-coping). We also test moderation and mediation effects directly using the SPSS PROCESS command; the mediation analyses include bootstrapping.

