### Effect moderators

The association between PNMS and health outcomes may not be simple and linear, as a number of factors may moderate the effects of PNMS on the woman and her unborn child.

Maternal psychosocial variables may be found to moderate the effects of PNMS. For example, considerable literature debates the “social support buffering hypothesis” [29], the idea that effects of a life event will differ according to the degree of social support. There is also an extensive literature in psychology demonstrating that various styles of coping with a life event, emotion-focused versus problem-focused [30, 31], will impact on the subsequent distress experienced. For example, problem-focused coping tends to increase an individual’s self-efficacy and control, and to reduce anger, anxiety, stress, and physiological arousal [32, 33].

The timing of PNMS appears to be an important moderator of PNMS effects on the fetus. It may be less the *type* of disruption to fetal neural development and more the *timing* in utero that determines risk for negative outcomes [34]. Timing effects are a function of (a) the ontogeny of fetal development, (b) alterations in maternal biological and psychological reactivity to stress during pregnancy, and (c) fetal exposure to stress-related biological processes through placental function (e.g., production of CRH) and/or placental transfer of, for example, cortisol [35].

It is also feasible that both maternal and fetal genetics moderate the effects of PNMS on the HPA axis, especially following events that are novel and uncontrollable [36]. In the current project, we focus on the maternal-placental-fetal (MPF) axis because it serves as a prototypical system with well-defined physiological inter-relationships to specify how we analyze interactions between maternal and fetal genotypes, and the environment.

*In utero* stress exposure may have sex-specific outcomes [8, 37-41] with some studies suggesting greater vulnerability in males, and others in females, depending on the outcome measured. Also, in rodents and humans, the activity and sensitivity of placental 11-βHSD2 to stimuli appears to be sex-linked, with greater vulnerability in males, which may partly explain the sex specificity of some stress-induced phenotypes [42].

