### The 2011 Queensland floods, the M@NGO trial, and QF2011

The Australian state of Queensland experienced severe flooding, the worst in 30 years, in early-January 2011 affecting more than 200,000 people in more than 70 towns. Three quarters of Queensland was declared a disaster zone with more than $1 billion of reported damages: flooding reached its peak in the state capital of Brisbane on January 10th. Residents of 2,100 Brisbane streets were told to evacuate and 20,000 homes were inundated. Approximately 35-40 deaths have been attributed to the floods. Two studies have published results on the effects of these floods on the perceived physical and mental health of residents. Researchers using random-digit dialing telephone surveys of more than 6,000 residents between March and June of that year found that 62 % of respondents reported being affected by Queensland’s severe summer weather events “in any way”, including property damage (as much as 37 % for those in some suburbs), with 2 % living elsewhere at least temporarily [60]. Income was reduced for 17 % of respondents. Trauma impacts ranged from feeling “terrified, helpless or hopeless” (14 %) to thinking they might be “badly injured or die” (4 %). Up to five months after the summer disaster, 7 % of respondents reported being “still distressed” and 9 % were “worried about how they would manage”. Results from a self-report postal survey (n = 960) conducted in July 2011 indicated that having been directly impacted by the floods (i.e., residence or vehicles affected by flood waters) was associated with increased risk of worse overall (OR = 5.3) and worse respiratory (OR = 2.3) health, greater psychological distress (OR = 1.9), and problems sleeping (OR = 2.3), and with symptoms reflecting probable post-traumatic stress disorder (PTSD) (OR = 2.3) [61, 62]. As response rates from both studies were less than 50 %, results are not generalizable to the entire population. Nonetheless, these results suggest that the Queensland floods of 2011 had significant impacts on health, including distress in the general population; nothing is known from these studies about effects on pregnant women, however.

The QF2011 Queensland Flood Study was designed to address the shortcomings of Project Ice Storm and other PNMS research. QF2011 subjects were recruited either through a pre-existing clinical trial or, after the floods, directly into the study outside of the clinical trial.

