## Methods/design: QF2011

### Participants

All women who agreed to participate in the study provided written informed consent. Inclusion and exclusion criteria differed slightly for M@NGO [63, 64] and for QF2011. Women were eligible for recruitment to the M@NGO trial if they were less than 24 weeks pregnant and were not planning caesarean section birth; QF2011 participants had to have been pregnant with a singleton pregnancy (at any gestation) and residing in the general vicinity of Brisbane on January 10, 2011. All participants were 18 years of age or older at recruitment, and were able to speak English fluently.

Recruitment for QF2011 began as soon as ethics approval was received (April 4, 2011), and continued to mid-January 2012 (12 months after the peak of the flood); as per original protocol, recruitment for M@NGO ceased on May 31, 2011 in both Sydney and Brisbane. Recruitment proceeded in 4 ways:When new participants were recruited into M@NGO, they were also presented with the QF2011 protocol, and invited to participate in either or both studies. M@NGO recruitment at the Mater Hospital involved face-to-face, phone, and e-mail recruiting following a routine mail-out describing the study to all women attending the antenatal clinic.The team contacted all existing M@NGO subjects who were eligible for QF2011 first by e-mail, then by cell phone (text message), then by telephone inviting them to also participate in the new flood study.The team invited women who were pregnant and eligible for the QF2011 study, but not eligible for M@NGO, or who would have been eligible for M@NGO but were approached after M@NGO recruitment ceased, to participate in QF2011. A flyer inviting women to participate and to contact the recruitment team was included in the routine mail-out from the antenatal clinic. A researcher in the antenatal clinic actively recruited participants face-to-face on site and was available to speak to midwives and other potential participants about the study.Finally, advertisements were placed in local newspapers, on radio, and on the internet for women who were pregnant at the time of the floods (even if they had already delivered).

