A number of women were recruited into QF2011 more than 10 months after the floods (n = ~50). Given that a 12-month post-flood questionnaire was planned, which repeated the administration of the recruitment questionnaire, the steering committee chose to send these women a single questionnaire at 12 months post flood rather than have them repeat the same questionnaire 2 months apart. As such, these women lacked a “recruitment IES-R” score. In order to impute these missing values, multiple regression was used to estimate their recruitment IES-R scores from post flood questionnaire responses. We used the dataset of women who had completed both the recruitment and the 12-month post flood questionnaires, and created separate algorithms for each IES-R sub-scale (Intrusions, Avoidance and Hyperarousal). Using this set of complete data, we regressed each recruitment IES-R sub-scale score on 12-month post-flood IES-R sub-scale scores, and other related scores that maximized the variance explained (STAI, PDI, PDEQ, MHC, etc.). The models explained 35.5 % (Avoidance), 44.2 % (Intrusions), and 49.1 % (Hyperarousal) of the variance in the recruitment scores. The regression coefficients from these results were used to create the equations we used for imputing the missing IES-R sub-scale scores for women who had not completed a Recruitment questionnaire. Once the sub-scales had been successfully imputed, IES-R Total scores were computed as usual by summing the sub-scales.

Maternal psychological health, psychosocial factors and other maternal measures

*Maternal anxiety (recruitment, 12 months post-flood, 6-12 weeks, 6 months, and 2½ years)*

The State-Trait Anxiety Inventory (STAI; [97]) is a valid and reliable self-report measure of how one generally feels (trait) or currently feels (state). We administered the State scale of the STAI at recruitment, 12 months post flood, and at 6-12 weeks and 6 months. At 2½ years we administered the Trait scale of the STAI. Each scale has 20 items and participants are asked to rate statements (e.g., “I am happy” and “I lack self-confidence”) on a 4-point Likert scale (rated from Almost Never to Almost Always).

*Depression (6-12 weeks and 6 months postpartum)*

As noted in the M@NGO protocol section, the EPDS (Edinburgh Postpartum Depression Scale) was administered as part of M@NGO to assess maternal depression in pregnancy and again at 6-12 weeks and 6 months postpartum.

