*Depression, Anxiety and Stress Scales (16 months, 2½ and 4 years)*.

For maternal mental health at later assessments, we administered the 21-item short form of the Depression Anxiety Stress Scales (DASS-21 [98-100]) which has three independent scales (i.e., anxiety, stress, and depression) and has been used widely in perinatal samples.

*Maternal depression (2½ years)*

Maternal depression was also assessed with the Centre for Epidemiologic Studies Depression Scale *(*CES-D; [101]) screening questionnaire. This is commonly used to assess feelings of depression in the general population. Women rated 20 statements (e.g., “I felt that I was just as good as other people” and “I felt depressed”) for how they felt during the past week on a 4-point scale ranging from “Rarely or none of the time (<1 day)” to “Most or all of the time (5-7 days).”

*Positive mental health (recruitment and 12 months post-flood)*

Positive mental health was assessed with the 14-item Mental Health Continuum – Short Form (MHC-SF [102]), which provides scores on Social, Emotional, and Psychological Well-Being. This scale has excellent psychometric properties. Extreme scores on this scale can define subgroups of “flourishing” and “languishing”.

*Coping style (recruitment, 12 months post-flood, 16 months, 2½ years, and 4 years)*

The Brief COPE includes 28 items: two items for each for the 14 coping strategies [103]. The Brief R-COPE assesses the frequency of 14 religious coping strategies which load onto positive and negative religious coping factors [104].

*Prior trauma (12 months post-flood)*

Because we have found that childhood trauma is associated with lower diurnal cortisol values in adulthood [105], women were asked to complete the Childhood Trauma Questionnaire (CTQ; [106, 107]), and the 24-item Trauma History Questionnaire (THQ; [108]) when the second set of salivary cortisol samples was taken. The CTQ provides information concerning instances of emotional, sexual, and/or physical abuse and emotional and physical neglect occurring before age 18 years. The THQ assesses whether individuals have experienced traumatic events such as crime, disasters, and physical or sexual assault after the age of 18.

*Life events (6 months and 16 months, 2½ years, and 4 years)*

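### Coping is tested as a moderator of flood exposure although it was only ever measured after the flood, in a model without a squared exposure term; if coping tracks exposure and the exposure effect is curved, the interaction test can be too liberal

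*Protocol article*

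**What the plan says.** In Maternal mental health (under Data analysis and power) the plan states: "We will test the ability of maternal coping style (Brief COPE) and specific candidate genes to moderate the effects of objective stress exposure". The outcomes are 12-month anxiety, PTSD symptoms and positive mental health. The method is hierarchical linear regression in a stated order: genotype and demographics, then objective stress (QFOSS), then peritraumatic distress and dissociation, then the psychosocial variable (coping is the example), and last one product term at a time. No squared exposure term is named.

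The timing of the measure is given as "Coping style (recruitment, 12 months post-flood, 16 months, 2½ years, and 4 years". Table 1 agrees: Brief COPE is a QF2011 instrument only, with no administration before QF2011 recruitment. On the dates, "flooding reached its peak in the state capital of Brisbane on January 10th" and "Recruitment for QF2011 began as soon as ethics approval was received (April 4, 2011), and continued to mid-January 2012". For late entrants, "A number of women were recruited into QF2011 more than 10 months after the floods (n = ~50"), and the decision was to "send these women a single questionnaire at 12 months post flood".

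The opening of Data analysis and power ties moderation by maternal characteristics to those that existed before the disaster. The test of depression as a moderator is limited to women with an EPDS score from before the floods. Coping has no matching restriction, and none is possible.

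**The concern.** A moderator is easiest to interpret when exposure could not have changed it. Here coping is recorded 12 weeks to 12 months after exposure. If women with more hardship also report more (or less) coping, coping carries information about exposure, and the product of exposure and coping contains a piece of exposure squared. A linear model with no squared term then credits curvature in the exposure effect to the product.

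Two things are at stake. First, the interaction test may reject more often than its nominal level. Second, a significant product could be read as a pre-existing coping style changing how exposure acts, when coping was never observed before exposure.

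The plan treats non-linearity as possible. Its trend analyses in Maternal short-term response to the floods cover associations among QFOSS, appraisal, PDI, PDEQ, IES-R and cortisol. They do not cover STAI or MHC-SF, and no result from them is carried into the moderation model.

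**Working it through.** **Timing.** 10 January to 4 April 2011 is 84 days, and 84 / 7 = 12.0 weeks. That is the earliest any Brief COPE could be completed. For the roughly 50 women with a single questionnaire, coping and outcome come from the same 12-month form. They are about 50 / (108 + 122) = 50 / 230 = 22% of the sample.

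**No figure to reproduce.** The article gives no sample size, error rate or exposure-coping correlation for this test. Everything below rests on assumed inputs: two-sided 5% level, 180 analysed women, and no true interaction.

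**Why the product picks up curvature.** Let X be standardised exposure and C standardised coping with correlation r, both normal. Then Cov(X², XC) = 3r − r = 2r and Var(XC) = 1 + r². If the true model has a term b·X² that is left out, the expected product coefficient is b·2r / (1 + r²), with standard error about 1 / √[n(1 + r²)] in residual SD units.

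- r = 0.2, b = 0.10: 0.10 × 0.4 / 1.04 = 0.0385; SE = 1 / √(180 × 1.04) = 0.0731; ratio 0.53; rejection about 8%.
- r = 0.5, b = 0.15: 0.15 × 1.0 / 1.25 = 0.12; SE = 1 / √(180 × 1.25) = 0.0667; ratio 1.80; rejection about 44%.

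The approximation ignores the leftover curvature in the residual. Simulation gives about 8% and 40% for these two corners.

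**Simulation without the peritraumatic block.** 3,000 runs per cell, r = 0.3, curvature expressed as a share of outcome variance, rejection of the product term:

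| Curvature | n = 230, normal | n = 230, gamma-skewed | n = 180, normal |
|---|---|---|---|
| 1% | 10.9% | 11.6% | 9.9% |
| 2% | 17.0% | 22.3% | 14.9% |
| 5% | 34.3% | 38.7% | 30.2% |

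With no curvature the rate is about 5% at any r. With r = 0 and n = 230 it rises only to about 8% (normal) or 11% (skewed) at 5% curvature.

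**Simulation with the peritraumatic block, as the plan specifies.** n = 180, r = 0.2 to 0.5, b = 0.10 to 0.15:

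| Share of curvature passing through peritraumatic distress | False-positive rate |
|---|---|
| None | about 8-40% (normal), 13-52% (gamma-skewed) |
| Half | about 5-18% |
| All | about 5% |

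The shape of exposure matters: a log-normal exposure (sigma 0.5) raises the upper end of the half-way case to 26%.

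**With X² added** before the product, the rate returns to about 5% in every setting. Coping squared is not needed.

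**Direction.** For an adverse outcome, a positive r with a flattening exposure effect gives almost only products with a protective sign (34.27 of 34.33 percentage points at r = 0.3, 5% curvature, n = 230). A negative r with an accelerating effect does the same. The other two combinations look like exacerbation.

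**The case against.** The strongest reply is that the conditions are not in the documents, and this largely stands. A reader might infer that coping depends on exposure. No passage says so. Effect moderators speaks of "various styles of coping with a life event" as something that shapes later distress, which is the opposite direction. Repeating the scale up to child age 4 years fits a general style at least as well as a reaction to the flood, and the article does not say which way the items were worded.

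A reader might also take the survey statement that "62 % of respondents reported being affected by" the summer weather, leaving 38% unaffected, as evidence of dependence. It cannot serve: it is a general-population telephone survey with no coping measure, and the article itself says such results do not generalise and tell nothing about pregnant women.

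It would also be too strong to say that mild curvature makes the interaction significant. Even with all curvature bypassing the peritraumatic block, most normal-exposure runs are non-significant, and if that block carries the curvature there is no inflation. The explanatory model does posit that exposure acts through peritraumatic responses.

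Nor do the documents plan to call coping a buffer or to recommend a coping style; they say only that it may moderate.

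Finally, the section presents its methods as a sample of approaches, allows psychosocial variables to be mediators as well as moderators, and enters coping after exposure. Those points soften the criticism. They do not remove it: the block order is stated, it ends in this product, and the trend analyses do not protect the test for every outcome.

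**Conclusion.** The point holds in conditional form. It is certain that no woman has a pre-flood coping score, that the earliest measurement is 12 weeks after exposure, that for about 50 women coping and outcome are taken together, and that the stated model has no squared exposure term. It is plausible but unquantified that coping varies with exposure. The size of the inflation rests on assumed values of the correlation, the curvature, the exposure distribution, the analysed sample and the route of the effect. It ranges from none to a several-fold excess over 5%. Apart from any inflation, the timing alone means a significant product cannot be read as the effect of a pre-existing style. This is a worthwhile, inexpensive improvement to a stated model rather than a flaw that invalidates it.

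**What to change.** 1. Enter QFOSS squared before any QFOSS-by-coping product.
2. Report the association between QFOSS and each coping score used, so that readers can judge how far coping tracks exposure.
3. Describe a product that survives as exposure by post-flood coping, not as moderation by a pre-existing style.
4. Keep the women without a recruitment questionnaire in the main analysis, and add a sensitivity analysis limited to recruitment Brief COPE. Making that restriction the main analysis would lose about 22% of the sample.

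Cost: one degree of freedom, a slightly less powerful interaction test, one extra reported association and one sensitivity analysis. The squared term removes the curvature artefact only; it does not turn coping into a pre-exposure variable, which is why the wording change is needed as well.
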